**B4. POSSIBLE BENEFITS**

Study subjects may experience improvement in their GERD and/or dyspeptic symptoms by participating in this study. The placebo response in GERD-related trials may be as high as 40% (Cremonini). Participants will also be remunerated for their time. More generally, this study will provide preliminary effect size estimates and may further our understanding of the effects of this supplement (Acidil) and elements that contribute to the placebo response in GERD.

**B5. POSSIBLE RISKS AND ANALYSIS OF RISK/BENEFIT RATIO**

Homeopathic medicines are generally regarded as relatively safe due to the low concentrations of active ingredients present. In the case of Acidil, all of the included substances are at a 4C potency, the equivalent of a  $10^{-8}$  dilution from the original starting concentration. Per Boiron, the manufacturer of Acidil, in reviewing their pharmacovigilance data, there have been no adverse event reports for this product over the past 10 years in the United States.

Nonetheless, some potential risks to subjects are as follows:

- a) Homeopathic practitioners describe a phenomenon known as “proving” in which a patient begins to experience worsening of symptoms after an initial improvement. This is thought to occur when a patient has received too much medication and the problem usually resolves when the patient stops taking the medicine or takes it less frequently.
- b) Questionnaires about symptom frequency and severity and quality of life: behavioral data collection involves virtually no risk, however, psychosocial tests may cause minor emotional distress. Because participants are free to stop at any time and will be reminded of this throughout the assessment process, the risk of distress is low. In our experience, behavioral tests are well tolerated and complications are extremely rare.
- c) Some subjects may experience distress knowing that they are being video or audio recorded. If this is the case, they may decline this portion of the study without being disqualified from further participation. The risk of breach of confidentiality of this data is low as all audio and video data will be collected and stored digitally on a password protected server.
- d) Keeping all data in locked files and stored on BIDMC hard drives that are behind a secure firewall will minimize the risk of inadvertent release of participant data. Participant data will be stored in de-identified form and will be identified only by study ID number. Corresponding participant names and PHI will be kept by the PI in a separate locked file.

**Overall, the potential risks to participants are modest and are likely to be viewed as reasonable in relation to the anticipated benefits to subjects and others.**

Any adverse event will be reported to the BIDMC IRB. In addition, we will convene an independent

monitoring committee approximately half way through subject recruitment to review study safety. The committee will be comprised of two individuals who are not involved in the study and have no substantive conflicts of interest. If, after reviewing the data, they feel there is evidence suggesting potential harm that warrants early termination of the study, the study will be stopped.

## **B6. RECRUITMENT AND CONSENT PROCEDURES**

### **Recruitment**

Subjects will be recruited initially from BIDMC HCA and GI clinics, but may eventually be recruited from other locations in the city. Additional locations may include local health food stores, the Marino Center (an integrative medicine clinic with sites in Sommerville and Waltham), and BIDMC-affiliated community primary care clinics. Permission to recruit study participants will be obtained from each site individually. Initial recruitment efforts will rely upon posted flyers (Appendix E). If the response to posted flyers is too slow, we will ask physicians to consider sending letters (Appendix E) to patients who may be eligible to introduce the study. Letters will be signed by both the patient's physician and study PI.

Flyers and letters will direct potential study participants to call a dedicated study phone number if they wish to receive further information about the study. Interested individuals will undergo a brief telephone screen to assess eligibility as described in Appendix A. Study calls will be returned 10am-9pm Monday thru Friday and 10am-5pm Saturday and Sunday, unless the caller specifically requests a call back outside of this time. If deemed ineligible to participate in the study, individuals will be referred back to their physician if they are seeking further care. If eligible, they will be sent a baseline symptom diary and scheduled for an intake visit as described above.

### **Consent**

Written informed consent will be obtained by the research assistant or study physician at the initial visit in the BIDMC GCRC after reviewing inclusion and exclusion criteria, the participant's symptom diary, and the online medical record (OMR) if the participant is a patient at BIDMC. Subjects will be asked to participate in a study examining the effect of a natural supplement containing a low dose combination of 4 herbs on heartburn and GERD-related symptoms. There will not be any specific mention of an intent to understand how the doctor-patient interaction or beliefs and expectations affect response to treatment. Informed consent will be obtained using the following process:

- The subject will be asked to review the study consent form;
- A member of the research staff will meet with the subject to review the form, to confirm the subject's understanding of the study, and to answer any questions that the subject might have; and
- Once the subject demonstrates understanding of the study and agrees to participate in the study, the consent will be signed by both the subject and research staff member.
- The consent form will allow subjects the opportunity to specifically decline audio and/or video recording of their interaction with the study physician.

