### B3. DESCRIPTION OF RESEARCH PROTOCOL

#### A. Study Design – Overview, Methods, Procedures

##### Overview

We propose to conduct a single-center, pilot feasibility, 2x2 factorial design randomized controlled trial assessing the effect of a homeopathic supplement (Acidil) and components of the placebo response (doctor-patient interaction and beliefs/expectations) on symptoms and HRQL in patients with GERD over a 2 week time interval. The Acidil vs. placebo intervention will be double-blinded and the standard vs. expanded interview intervention (doctor-patient interaction) will be single-blinded. Randomization will be by permuted block randomization with block sizes of 4 and 8. We plan to enroll 6 patients into each group for a total of 24 subjects in the study according to the adjacent scheme. Subjects will be evaluated in the GCRC at BIDMC at two timepoints: baseline and at 2 week follow-up.

|                    | Acidil  | Placebo |
|--------------------|---------|---------|
| Standard Interview | Group 1 | Group 2 |
| Expanded Interview | Group 3 | Group 4 |

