#### First Study Visit (Time 1):

When a potential subject arrives at the study site, the diary will be reviewed to ensure that it meets eligibility criteria (symptoms at least 3 days out of 7 and symptom frequency and severity recorded on at least 6 days of 7) and the individual will undergo a final in person eligibility assessment reviewing the criteria discussed during the phone screen. Subjects deemed ineligible will be thanked for their effort, informed that they are not eligible, receive parking validation and be dismissed.

Eligible subjects will be formally consented, have blood drawn (if they opt to participate in the repository study described in a separate application), and complete a series of baseline questionnaires (demographics, medication and supplement use, GSRS, Nepean Dyspepsia Index, GERD-HRQL, SF-12, MYMOP, credibility questionnaire, CAMBI, see Table 1 below). Next, subjects will be randomized to one of the 4 treatment groups and receive either the standard or expanded interview in a single-blinded fashion (the study physician will be aware of assigned interview type, but the subject will not). The clinical interview will be audio and video recorded (pending subject permission) to permit subsequent assessment of fidelity to the treatment protocol.

After the interview, subjects will complete additional questionnaires (CARE, credibility questionnaire, see Table 1). Finally, subjects will receive the study medication (Acidil or placebo) in a double-blinded fashion (neither the study physician nor the subject will be aware of treatment assignment) and rescue antacid. The study physician, or another member of our research team, will provide medication education. All subjects will receive the same instructions for how to take the study medication and rescue antacid, will be provided with a new study diary, and their 2 week follow-up appointment will be confirmed. Study subjects will be contacted 7 days following the first study visit to confirm that they are taking the study medication, completing their daily diary, and not experiencing any marked adverse effects. The first study visit is anticipated to last 1-2.5 hours.

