#### Intervention and Control Groups:

##### *Standard and Expanded Intake Groups*

Subjects assigned to groups 1 and 2 will receive a standard allopathic clinical interview (Appendix B) by the study physician inquiring into the nature and history of their GERD and dyspeptic (if present) symptoms and prior and current treatments undertaken to control symptoms, including any complementary treatments. The study physician will also review the subject's symptom diary and the study questionnaires completed immediately prior to the interview and conduct a brief physical exam. The interview is expected to last 20-30 minutes.

Subjects assigned to groups 3 and 4 will receive an expanded clinical interview (Appendix B) by the study physician similar to the type of interview performed by classical homeopathic physicians. In addition to the above evaluation, the expanded interview will also include questions inquiring about any additional symptoms or diagnoses that the subject currently has, the subject's temperament, likes and dislikes, effects of weather on symptoms, and sleep. The expanded interview is expected to last approximately 1 hour, though for medically complex patients it could last as long as 1.5 hours.

The same study physician ([name]) will be conducting all study interviews and thus will not be blinded to this aspect of study group assignment, but will remain blinded to study medication assignment. [name] has been receiving training in classical homeopathic case taking and analysis and will thus be able to mimic the types and depth of questions typical for a homeopathic consultation. As this aspect of the intervention is primarily about the length of time spent with the subject, and depth of questions asked, there will be no overt attempt to vary the amount of empathy between the two

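### Allocation concealment for the interview factor (Aim 3) is not protected: the physician who knows every earlier interview assignment is allowed to take consent before randomization

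*Protocol*

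**What the plan says.** The Overview (B3.A) describes a "single-center, pilot feasibility, 2x2 factorial design randomized controlled trial" and adds: "Randomization will be by permuted block randomization with block sizes of 4 and 8". It sets the size as follows: "We plan to enroll 6 patients into each group for a total of 24 subjects in the study".

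Under Standard and Expanded Intake Groups, a single named physician "will be conducting all study interviews and thus will not be blinded to this aspect of study group assignment". First Study Visit (Time 1) confirms that "the study physician will be aware of assigned interview type, but the subject will not".

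The same section gives the order of events at visit 1: diary check and final eligibility review, consent, baseline questionnaires, randomization, interview. On eligibility it says "the individual will undergo a final in person eligibility assessment reviewing the criteria discussed during the phone screen", without naming who does the assessment.

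The Consent section (B6) does name roles: "Written informed consent will be obtained by the research assistant or study physician at the initial visit". It places that step "after reviewing inclusion and exclusion criteria", the diary and, where available, the medical record.

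Testing and Outcome Measures says that testing is done by staff blinded to treatment assignment, with the physician's knowledge of interview type as the exception. The protocol names no holder of the sequence, describes no concealment method, and has no rule separating the physician from consent or eligibility.

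**The concern.** Randomizing after consent prevents foreknowledge only if the person admitting subjects cannot work out the next assignment. Here one person sees the interview type of every earlier subject in a single running sequence, can read the block sizes in the protocol, and may be the one who admits the next subject. Each block holds equal numbers of standard and expanded interviews, so past assignments carry information about the next.

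For Aim 3, the stake is selection. Someone with a hunch about the next interview type can, without bad faith, encourage one person a little more than another, read a judgement-based exclusion differently (predominantly dyspeptic symptoms, significant swallowing difficulty, uncontrolled psychiatric disease), or rebook a visit. The standard interview takes 20-30 minutes and the expanded one about an hour, or up to 1.5 hours for medically complex patients, which gives an ordinary practical reason to do so.

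The outcomes are self-reported, and for Hypothesis 3c the protocol says the sample is too small to adjust for confounders. The stated purpose is to supply preliminary effect sizes for a larger trial, and selection would distort exactly those.

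**Working it through.** The protocol gives no figure for predictability, so there is none to reproduce.

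**Inputs from the protocol.** One centre; 4 groups of 6, total 24, hence 12 standard and 12 expanded; permuted blocks of 4 and 8; one physician aware of every interview type.

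**Assumptions.** Each block is balanced over the four groups, so a block of 4 holds 2 standard and 2 expanded interviews and a block of 8 holds 4 and 4. Where the order of block sizes matters, 4 and 8 are equally likely and in random order.

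**Step 1: block size known.** The guesser always names the interview type that is behind in the block, and tosses a coin when they are level. For a block of 2m, the expected proportion correct is

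[m + 4^m / (2·C(2m, m)) − 0.5] / (2m)

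- Block of 4 (m = 2): [2 + 16/12 − 0.5]/4 = 2.833/4 = 70.8%.
- Block of 8 (m = 4): [4 + 256/140 − 0.5]/8 = 5.329/8 = 66.6%.

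Enumerating all sequences within a block gives the same values. It also gives the share of assignments that are fully determined: 1/3 in a block of 4 and 1/5 in a block of 8. Over simulated lists of 24 this comes to about 5.7 certain assignments.

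**Step 2: order of block sizes unknown.** With 20,000 simulated sequences of 24 and an optimal Bayes guess from past interview types:

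| Quantity | Result |
|---|---|
| Correct guesses | 67.5% (about 16 of 24, against 12 by chance) |
| Assignments that are certain | about 1.7 of 24 |
| Assignments callable with probability 75% or more | about 9.5 of 24 |
| Sequences with at least one certain assignment | 66% |

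Hiding the order therefore removes most of the certainties but leaves the average guess rate near 67%.

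**Step 3: what this could do to the estimate (illustrative).** Suppose every admitted subject's prognosis is shifted by +η or −η SD according to the guess. The expected difference between interview arms is 2η(2 × 0.675 − 1) = 0.70η. For 12 v 12 the SE of a difference in means is √(2/12) = 0.408 SD. Two-sided type I error is P(|Z + 0.70η/0.408| > 1.96).

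| η (SD, assumed) | Bias (SD) | Type I error |
|---|---|---|
| 0.05 | 0.035 | 5.1% |
| 0.10 | 0.07 | 5.3% |
| 0.25 | 0.175 | 7.1% |
| 0.50 | 0.35 | about 14% |

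Nothing in the protocol fixes η. The calculation also treats the outcome as a continuous score, whereas Hypothesis 3a uses a binary responder outcome in a logistic model.

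**The case against.** A reader might infer that concealment has failed, that is, that the physician does admit subjects knowing their arm. The documents do not support that. The physician's consent role is permitted, not required. The consent steps refer to a member of the research staff, and no assessor is named for the final eligibility check. With the order of block sizes unknown, most guesses are no more than likely, and fewer than two of 24 are certain.

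A reader might also take a type I error of 7-14% as the size of the harm. That needs a shift of 0.25-0.5 SD for every subject. If the shift came only from turning people away, a physician who predicted a normally distributed prognosis perfectly would have to reject about 13% of attenders for 0.25 SD (24 × 0.13/0.87, about 4 extra people) and about 30% for 0.5 SD (24 × 0.30/0.70, about 10). With a correlation of 0.5 between judgement and prognosis, it would be 30% to 62%. Smaller shifts are at least as plausible, and they leave the error close to 5%.

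Other points narrow the route. Subjects make first contact, are screened by telephone and are booked in advance. The diary rule is numeric. Beliefs and credibility are first measured before randomization, so an imbalance in them would be visible. Feasibility is the primary outcome, and low power is acknowledged.

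All of this limits the size of the problem. It does not close the gap. The physician is expressly allowed in the consent step, several exclusions need judgement, and pilot status does not protect effect estimates that are meant to be carried into a larger trial.

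**Conclusion.** The point holds as a gap in protection. The protocol lets the one person who knows all earlier interview assignments review eligibility and take consent before randomization, with the block sizes disclosed. The next interview type is then predictable about 67% to 71% of the time instead of 50%. These rates rest only on balanced blocks and, for the 67.5% figure, on equally likely sizes in unknown random order. If the order were fixed or known, predictability would be higher.

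The effect on the estimates is unknown. Under assumed shifts of 0.05 to 0.5 SD, type I error runs from about 5% to 14%, as illustration only. Only Aim 3 is exposed. A reader might extend the worry to Acidil v placebo, but the physician stays blinded to the medication, so past assignments say nothing about it. Stratifying by PPI/H2 blocker use, if Subject Selection triggers it, would not remove the problem, because the physician could follow each stratum.

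This is a matter of trial conduct that the protocol itself fixes, and it is cheap to correct.

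**What to change.** 1. In the Consent section, remove the study physician from those who may obtain consent.
2. In the Consent section and First Study Visit (Time 1), state that diary review, the final in-person eligibility sign-off and consent are completed before the allocation is opened. They should be done by the research assistant or another existing team member who is neither told nor able to observe earlier interview assignments. This fits the staff blinding already stated under Testing and Outcome Measures and brings expected guessing back to 50%.
3. As a minor addition, keep the block sizes and their order out of documents the physician sees. On its own this is not enough, since guessing would stay near 67%.

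The cost is protocol wording. The downside is practical: the research assistant must attend each first visit and must be kept from seeing interview type or length. Otherwise the gap between 20-30 minutes and about an hour would only move the foreknowledge from one person to another.

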### **Subject Protection**

Subjects may withdraw from the trial at any time and they will be informed that the study is entirely voluntary and that their clinical care will not be affected by this action. We will not specifically seek to enroll specific vulnerable populations.

**B7. STUDY LOCATION****Privacy**

Initial screening for the study will occur by telephone and will require potential subjects to initiate the process by calling the study phone number and indicating an interest in participating in the study. This process will not require extensive discussion of sensitive information. Formal consent to participate will occur in the GCRC in a private setting. All anthropomorphic (e.g., height and weight) and questionnaire data gathered as part of the study as well as conversations with the study physician discussing symptoms will also occur in a private setting in the GCRC. In all cases, the information gathered will be limited only to the data necessary to accomplish the research purposes.

**Physical Setting**

All subject interviews and testing will occur in the BIDMC GCRC except for circumstances in which the subject cannot return for the follow-up visit and elects to complete the second set of questionnaires from home or over the telephone.

**B8. DATA SECURITY**

All written/questionnaire data will be stored in a locked file cabinet in the study physician's office, which itself is locked whenever no one is present in the office. The only identifier that will be present on this data will be a unique, subject-specific study ID. This data will also be transferred to the password-protected database. We plan to utilize the REDCap system sponsored through BIDMC and the Harvard Catalyst Program. In addition, all computer files will be password protected. The study database will not include data items that uniquely identify participants such as subject name, address, phone number, social security number and medical record number, but will be indexed by subjects' study IDs. All data will be processed in aggregate form. The master list linking subjects' study IDs to personally identifiable information will be on file in a locked cabinet in the study physician's office. Electronic communication with outside collaborators will only involve deidentified information.

**B9 Multi-Site Studies**

Is the BIDMC the coordinating site or is the BIDMC PI the lead investigator of the multi-site study?

☐ Yes ☒ No *Not applicable. This is not a multi-site study.*

